### Data collection

The data for this study will be collected by the measures as outlined in Table 3, at three time points, by an assessor blind to group allocation (1): before the intervention period (pre-intervention) (2); following the completion of the 16-week intervention (post-intervention); and (3), at 12 weeks following the intervention (follow up), with follow up being the primary endpoint. Additionally, there will be an 8-week data collection point for the cost analysis study (mid-intervention) (Table 3).

**Table 3 Tab3:**
[figure not shown]
Schedule of enrolment, interventions, and assessments

Timepoints: *T1* baseline, *T2* mid-intervention, *T3* post-intervention, *T4* follow up. Involvement: *A* adolescent, *P* parent/carer, *R1* assessor blinded to the group allocation, *R2* assessor blinded to the hypothesis. Measures: *ADOS-2* Autism Diagnostic Observation Schedule - Second Edition, *CBCL* Childhood Behaviour Checklist; *CHU9D* Child Health Utility 9D, *CSIE* Circumplex Scale of Interpersonal Efficacy, *ERSSQ* Emotion Regulation and Social Skills Questionnaire, *GAS* Goal Attainment Scaling, *NEQ* Negative Incidents and Effects of Psychological Treatment, *PedsQL 4.0* Pediatric Quality of life Inventory, *PLS* Perth Aloneness Scale, *SIAS* Social Interaction Anxiety Scale, *SRS-2* Social Responsiveness Scale, *TSS-2* Treatment Satisfaction Scale, *TIC-P* Treatment Inventory of Costs in patients, *WASI-II* Wechsler Abbreviated Scale of Intelligence - Second Edition

Given this study will use an intent-to-treat approach, if participants are unable to finish the programme or attend the face-to-face assessment sessions, they will be contacted and encouraged to complete the questionnaires via email.

### Primary outcome measure

Goal Attainment Scaling (GAS) evaluates the outcomes and suitability of an intervention in an individual or group setting [58, 59]. Following the guidelines suggested by Kiresuk and colleagues (1994) adolescents randomized to both the treatment and control group, will establish at least three personally meaningful and measurable social goals in collaboration with an assessor blinded to the group allocation*.* The achievement of these goals will be scored via the GAS scoring system, whereby −2 indicates the participant’s current level of performance, −1 indicates less than expected, 0 indicates the expected progress, and +1 and +2 indicate progress above the expected level [60]. As suggested by previous research, the reliability of GAS will be calculated for this sample [54].

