### Design

This will be a stratified (gender, site), RCT of a the SSGT programme (KONTAKT©) compared to a manualised active control group (a cooking group “Super Chef”) with a ratio of 1:1, adhering to the CONSORT statement for conducting high-quality RCTs [48] (Fig. 1). Data collection will occur at three time points (1): at baseline, prior to randomization to intervention or control; (2) at post-test, immediately following the intervention period; and (3) at follow-up, 12 weeks following the intervention (primary endpoint).

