### Statistical analyses

As suggested by previous research, reliability of the GAS goals will be investigated via examination of their measurability, equidistance, and difficulty [57]. A random effects regression model will be used to explore those factors associated with the raw data on the GAS scores (dependent variable), over the 9-month duration of the study. Independent variables for the model will be time, group (KONTAKT© versus Super Che’), age, IQ, gender, centre, and comorbidity as fixed effects, with follow up being the primary endpoint of the study. The random effect will be the participant’s ID number, thus accounting for the correlation between measurements made on the same individual within the model.

Analysis of secondary outcomes (interpersonal efficacy, quality of life, social anxiety, loneliness, facial emotion recognition, and eye-tracking behaviour) will be conducted in a similar manner (random effects regression model). Analysis will be based on an intent-to-treat approach [84], considering each participant as belonging to the study group they were initially allocated, regardless of treatment actually received. Missing data will be accounted for according to the guidelines specified for each measure; if no guidance is provided, missing data will be handled in accordance with the CONSORT statement for conducting high-quality RCTs [48]. Data analysis will be conducted using the SPSS version 24 statistical software [88].

The outcomes of the present study will be compared to results obtained by previous evaluations of the short and long variant of KONTAKT© undertaken in Sweden.

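### Baseline GAS is −2 for everyone by construction; kept as an outcome row, it either dilutes the group effect or misstates the standard error at follow-up

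*Protocol article*

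**What the plan says.** All references are to the protocol article.

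- **Primary outcome measure.** Each adolescent "will establish at least three personally meaningful and measurable social goals". On the scoring scale, "2 indicates the participant’s current level of performance" (the figure carries a minus sign in the text). Zero is expected progress, and +1 and +2 are better than expected.
- **Design.** "Data collection will occur at three time points": baseline before randomization, post-test, and follow-up 12 weeks after the intervention. Follow-up is the primary endpoint. The Data collection section agrees.
- **Statistical analyses.** The model is a random effects regression on the "raw data on the GAS scores (dependent variable), over the 9-month duration of the study". "Independent variables for the model will be time, group", followed by age, IQ, gender, centre and comorbidity. No group-by-time term is listed. "The random effect will be the participant’s ID number", "thus accounting for the correlation between measurements made on the same individual within the model". Follow-up is again named as the primary endpoint.
- **Sample size calculations.** The minimum of 57 comes from a repeated-measures MANOVA for a within-between interaction at three time points.

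**The concern.** If the lowest score is defined as where the participant starts, a score taken when goals are set is −2 for every goal and every participant. It has no variance and no correlation with later scores. A random intercept with one residual variance assumes the opposite: equal variance at every visit and equal correlation between every pair of visits.

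The constant row says nothing about treatment, yet it would enter both the estimate and the variance components of the only primary analysis. Two things are at stake: whether the model estimates the follow-up difference that the protocol calls primary, and whether the standard error attached to that difference can be trusted.

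**Working it through.** **The plan's own figure.** For the interaction test with 2 groups and 3 measures, df1 = 2, df2 = N − 3 and λ = N × 0.54². At N = 57, λ = 16.6 and power is 0.953, so the stated 57 reproduces when 0.54 is entered as the MANOVA effect size f(V). The present point does not change that figure. It does show that an interaction was in mind at the design stage.

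**Inputs.** From the article: three visits, 1:1 allocation, 90 participants (45 per arm), and baseline fixed at −2. Assumed, because the article gives neither: variances v3 at post-test and v4 at follow-up, and their correlation ρ. The scale is set so that v4 = 1, and v3 = 1 unless stated. Calculations use one mean GAS score per participant, complete data and no covariates.

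**What the random intercept estimates.** True variances are (0, 1, 1), and the only non-zero covariance is ρ.
- Total variance = (0 + 1 + 1)/3 = 2/3
- Intercept variance = average covariance = ρ/3
- Residual variance = 2/3 − ρ/3 = (2 − ρ)/3

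**Reading A: main effects only, as listed.** The group coefficient is the arm difference averaged over three visits, and the baseline difference is fixed at 0.
- Effect d at both later visits: (0 + d + d)/3 = 2d/3
- Effect d at follow-up only: (0 + 0 + d)/3 = d/3
- Model variance of a participant's mean: ρ/3 + (2 − ρ)/9 = (2 + 2ρ)/9. The true variance of (Y3 + Y4)/3 is also (2 + 2ρ)/9, so the standard error is right. At ρ = 0.7 it is √[(2/45)(3.4/9)] = 0.130. Simulated type I error was 0.049–0.051.

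**Reading B: group-by-time added, arm difference at follow-up.** The model uses variance 2/3 where the truth is 1.
- Ratio of model to true standard error = √(2/3) = 0.816 at any ρ. With 45 per arm, √[(2/45)(2/3)] = 0.172 against √(2/45) = 0.211.
- Type I error = 2[1 − Φ(1.96 × 0.816)] = 0.110. Simulation (20,000 null trials per setting) gave 0.109–0.113.
- With unequal variances the ratio is √[(v3 + v4)/(3v4)]:

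| v3/v4 | SE ratio | Type I error |
|---|---|---|
| 0.5 | 0.707 | about 16–17% |
| 1.0 | 0.816 | about 11% |
| 1.5 | 0.913 | about 7% |
| 2.0 | 1.000 | 5% |

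**Reading C: group-by-time added, change from baseline to follow-up.** Model variance is 2(2 − ρ)/3. True variance is 1, because baseline contributes none. The ratio is √[2(2 − ρ)/3].

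| ρ | SE ratio | Type I error |
|---|---|---|
| 0.3 | 1.065 | 3.7% |
| 0.5 | 1.000 | 5.0% |
| 0.7 | 0.931 | 6.8% |
| 0.8 | 0.894 | 8.0% |

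**Baseline row removed.** With post-test and follow-up only and group-by-time fitted, the mean model standard error at follow-up is 0.210 against an empirical 0.210. Type I error is 0.049–0.050 for ρ from 0.3 to 0.8.

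**The case against.** The strongest reply has four parts.

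1. **The listed model has no group-by-time term.** Its group standard error is then correct. This stands: a reader might infer that the planned primary test runs at 11% type I error, and the text does not support that for the model as written. Reading A's test is also valid as a test of the post-test/follow-up average, since estimate and standard error are both scaled by 2/3. What it does not give is the follow-up difference on the GAS scale.
2. **The article never says outright that baseline GAS is an outcome row.** The schedule table is not shown, and the text speaks of scoring goal achievement. This stands as a limit on certainty. Modelling raw scores across the full nine months, with three visits including baseline, still makes inclusion the natural reading.
3. **Equal residual variance is not stated, and covariance detail is often left to an analysis plan.** This stands in part. The article names participant as the only random effect and says that this accounts for within-person correlation, but it does not exclude visit-specific residual variances. Readings B and C are therefore conditional on a common residual variance.
4. **The 0.82 ratio is one case.** Correct: it needs v3 = v4, and the tables above show the range. The model could also be fitted to goal-level rows, which these calculations do not cover.

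A reader might also infer that dropouts contributing only a baseline row make matters worse. The article does not say how such participants enter the model, so nothing here rests on that.

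**Conclusion.** The point holds in conditional form. By the protocol's own scale, baseline GAS is constant, and the most natural reading of the analysis section puts it into a random-intercept model as an outcome.

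- With main effects only, the standard error is sound, but the coefficient is 2d/3 or d/3 and is not specific to follow-up.
- With group-by-time, which both the sample size method and the follow-up endpoint imply, and a common residual variance, the follow-up arm difference has type I error of about 11% under equal variances. It is about 16–17% down to 7% for post-test/follow-up variance ratios of 0.5 to 1.5.
- For change from baseline under the same model and equal variances, type I error runs from about 4% to 8% for correlations of 0.3 to 0.8, and is correct at 0.5.

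It would go too far to say that the primary standard error is wrong whichever way the plan is read, or always too small. Each of these readings nevertheless leaves the declared endpoint poorly served: a diluted estimate that is not specific to follow-up, a standard error that is too small under equal variances, or one whose accuracy depends on an unknown correlation.

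**What to change.** In Statistical analyses:

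1. State that baseline GAS is not an outcome row because it is −2 by construction.
2. Model post-test and follow-up GAS only, with group, time, group-by-time and the listed covariates. Use an unstructured 2×2 covariance. A random intercept is acceptable, but it assumes equal variance at the two visits.
3. Name the group contrast at follow-up as the primary test.

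Keeping the baseline row and giving each visit its own residual variance is not an alternative. With zero baseline variance the likelihood is unbounded: as the intercept and baseline residual variances were set to 10⁻¹, 10⁻², 10⁻⁴ and 10⁻⁸, the log-likelihood rose from −14 to 88, 295 and 709. The random intercept is driven to zero and the post-test/follow-up correlation is lost.

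The cost is a change of wording. No information is lost, because a constant carries none. Secondary measures with a real baseline are unaffected and can keep it.

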### Secondary outcome measures

The Social Responsiveness Scale - Second Edition (SRS-2) standard version is a 65-item parent rating scale, designed to measure autistic-like traits in individuals aged 4–18 years. The SRS-2 enables calculation of a total score and five subscales: social awareness, social cognition, social communication, social motivation, and restricted interests and repetitive behaviour. The scale is scored on a 4-point Likert scale, ranging from “not true” (0) to “almost always true” (3). Scores range from 1 to 195 with the expected value for individuals with a primary diagnosis of ASD being approximately 100 [61]. Previous studies in individuals with ASD show good psychometric properties for SRS-2 (internal consistency of 0.9) [62, 63]. As recommended for research, the raw scores of the measure (total and subscale) will be used in this study [63].

The Circumplex Scale of Interpersonal Efficacy (CSIE) [64] measures an individual’s confidence in their ability to successfully perform behaviours associated with each facet of the interpersonal circumplex (assert, distance, yield, and connect). Each octant scale shows a progressive blend of two axial dimensions (e.g. “speak up” representing an assertive action, “get them to leave me alone” a distancing action, and “tell them when I am annoyed” combining these two actions) [65]. As suggested by previous research, this study will use these dimensional scores instead of the eight octants to predict the outcome [66]. Previous studies in adolescents with ASD have demonstrated acceptable internal consistency of 0.78 for this measure [64].

The Perth Aloneness Scale (PLS) is a self-report measure consisting of 24 statements such as “I feel left out of things at school”, or “I get along with my classmates”, measuring four dimensions of loneliness in young people (isolation, friendship, and positive and negative attitudes toward solitude) [67–69]. Responses are recorded on a 6-point Likert scale indicating agreement with a statement, ranging from “never” (1) to “always” (6), with higher scores suggesting higher levels of loneliness and negative attitude towards solitude. This scale has yielded good reliability for the overall scale and subscales (Cronbach’s alpha = 0.84). The use of the scale in the current study is further supported by established norms for Western Australian adolescents [67].

The Emotion Regulation and Social Skills Questionnaire (ERSSQ) is a 27-item measure assessing emotion regulation and competency in social skills [70]. The questionnaire is designed to measure frequencies of effective engagement in social behaviours (e.g. “chooses appropriate solutions to social problems” or “deals effectively with bullying”), examining the competency of these skills [70]. Responses are rated on a 5-point Likert scale, ranging from “never” (0) to “always” (4), yielding a total score of 0–108, with higher scores indicating higher competencies in social behaviour. ERSSQ has demonstrated good internal consistency for children with ASD (Cronbach’s alpha = 0.89) [70].

The Paediatric Quality of life Inventory ™, version 4.0 (PedsQL ™ 4.0) is a 23-item parent proxy report and an adolescent self-report measure of adolescent’s quality of life underpinned by the four subscales of physical, emotional, social, and school functioning [39, 71]. Responders rate items according to if they have been a problem for them, on a 5-point Likert scale ranging from “never” (0) to “almost always” (5), with lower scores indicating better quality of life. Although there is no ASD-specific module available, the questionnaire has high validity and reliability (Cronbach’s alpha = 0.97) and has been used in adolescents with ASD [12, 39], including Australia youths with ASD [72, 73].

The Social Interaction Anxiety Scale (SIAS) is a 20-item measure assessing adolescents’ self-reported anxiety in social situations, via items such as “I become tense if I have to talk about myself” or “I find it easy to make friends my own age”. Items are rated on a 5-point scale ranging from “not at all” to “extremely”. Total scores range from 0 to 80 with higher scores indicating greater anxiety in social situations. The scale has a good internal consistency and test-retest reliability (Cronbach’s alpha = 0.94) [74] and has been validated in an Australian setting in Australian adults [75].

The Child Health Utility 9D (CHU9D) is a 9-dimension health-related quality of life scale (worried, sad, pain, tired, annoyed, school work, sleep, daily routines and activities), designed to estimate the adolescent’s quality-adjusted life years (QALYs), providing a standardised measure of disease burden. The measure is rated on a 5-point scale with a “don’t” sentence linked with no problems (e.g. “I don’t feel sad today”) and “very” with the participant experiencing many problems (e.g. “I feel very sad”). Calculation of a universal score is supported by an adolescent-specific scoring algorithm, with 1 representing “full health” and 0 “death” [76]. Previous research suggests that the CHU9D supports appropriate calculation of QALYs [77].

Healthcare consumption and productivity loss will be measured via a tailored version of the Trimbos/iMTA questionnaire for patients with a psychiatric disorder (TiC-P), a well-established questionnaire examining health care usage and any work, education, and productivity losses incurred by participants and their carers. The modified version of the TIC-P employed in this study comprises six sections enquiring about healthcare visits, support received both at and outside of school, medications and supplements, work, and education and productivity losses incurred by both parents and adolescents. The feasibly of the inventory was evaluated in the KONTAKT© pilot study.

The Mindreading Battery enables assessment of facial emotion recognition accuracy [78], with this study measuring adolescents performance across 40 basic and complex emotions, over 6 developmental levels with level 1 being the simplest (e.g. happy) and level 6 being the most complex (e.g. exonerated) (Table 3). Emotions are displayed in the form of 2–5-sec silent coloured video clips, with four multiple choice options, one of which is the correct emotion label and three of which are distractor items. The distracter options were randomly selected from the entire Mindreading Battery emotion groups, excluding the emotion group from which the target stimuli originated. Further details of the stimuli are outlined in Table 4. During the presentation of stimuli, eye-tracking data will be recorded via a remote eye tracker device (RED) developed by SensoMotoric Instruments, enabling examination of fixation patterns and fixation durations [79]. While the eye tracker accommodates small head movements, a chin rest will be available to participants who find it hard to sit still. Outcome measures will be assessed in relation to accuracy, response time, and number of and duration of fixations to dynamically defined areas of interest including the eyes, nose, and mouth of the stimuli [80, 81].

**Table 4 Tab4:** Overview of the Mindreading Stimulus Battery

Stimuli characteristics	Number of stimuli items
Valence	
Negative	22
Positive	16
Gender	
Male (Pre)	17
Male (Post)	18
Female (Pre)	21
Female (Post)	20
Emotion level	
Basic	6
Level 1 and 2	6
Level 3 and 4	15
Level 5 and 6	11

The Negative Incidents and Effects of Psychological Treatment (NEQ) assesses potential adverse and unwanted events associated with attending the groups at the completion of each programme, via adolescent self-report [82]. The NEQ is a 32-item questionnaire requiring adolescents to quantify, on 5-point Likert scale with response options ranging from “not at all” to “extremely”, any negative events experienced during the intervention period, asking participants to attribute their causality to either the programme or external circumstances. Analysis of the measure has shown good reliability (Cronbach’s alpha = 0.95) [82].

The Experience Sampling Method (ESM) will evaluate adolescents’ everyday quality of life via daily responses from both adolescent and parent proxy report [83–85]. This 5-item measure, specifically designed for the purposes of this study, asks “In the last 24 hours, on a scale of 1 to 10 I have been feeling … ” with answers rated on a 10-point scale in five dichotomised emotional sets (sad/happy, lonely/unlonely, angry/calm, scared/unafraid, and anxious/confident). Questions are texted via mobile phones to adolescents and parents once daily from commencement of the groups to the final follow-up time point. The feasibility of this approach was assessed during a pilot study, with this method previously showing consistency across experiences and in examining the effect of social context on the daily experiences of adolescents with ASD [86].

The Treatment Satisfaction Scale (TSS-2) [87] is a short, 6-item parents’ and adolescents’ self-report instrument, measuring satisfaction with group attendance. Each item is scored on a 4-point Likert scale with response options ranging from “yes, very much” to “no”, with an open comment section, encouraging participants to freely share their experiences with the intervention.

Blind expert rating of social functioning will be assessed by an occupational therapist or psychologist, experienced in working with adolescents with ASD, and blinded to the study hypothesis, via a rating scale designed specifically for the purposes of this study. The scale requires a rating of participant’s social communication and interaction on a scale of 0–10 as observed during three video recordings of the snack times of sessions 2, 10, and 15 in both the intervention group and control groups presented in random order.

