### The interventions

In evaluating the feasibility and acceptability of KONTAKT© in an Australian context, a pilot version of the 16-session KONTAKT© was delivered to 16 adolescents meeting the inclusion criteria across 16 sessions in 20 weeks, with two 8-week session blocks interspersed with the Australian school holidays. After completing the KONTAKT© intervention, focus groups were held with participants, parents and trainers, capturing their perspectives of the programme. Following analysis of focus group data, final adjustments and modifications were made to the KONTAKT© 16-week variant, standardising the intervention in preparation for RCT evaluation. Tables 1 and 2 detail the structure and content of KONTAKT© (the opportunity to choose social themes/activities that reflect the participants’ personal goals or interests) and Super Chef (personal tastes for each recipe) sessions, and their emphasis on individualized activities aiming to promote motivation in the participants and generalization of skills [32].

**Table 1 Tab1:** The structure, objectives and individualized parts of weekly KONTAKT© sessions [57]

Rounds	Objective	Individualized activity
Opening	Warm-up activity, initiating conversation, promoting interaction between group members, promoting eye contact	
Reviewing homework	Reinforcing and providing feedback, troubleshooting if necessary	Sessions 2–15
Group discussion	Exchanging experiences, promoting social cognition and social relationship	Sessions 12–15
Group activities	Providing practical solutions and strategies for everyday challenging social situations, fostering a feeling of group cohesion, practicing cooperation, practising recognising and interpreting non-verbal signals, eye contact, and facial expressions	Sessions 12–15
Snack time	Practising small-talk and turn-taking in unstructured conversations	
Assigning new homework	Generalizing learnt skills to everyday social situations	Fixed: sessions 1–10 Flexible: sessions 11–14
Closing	Evaluating the session, promoting interaction between group members

**Table 2 Tab2:** The structure, objectives and individualized activities of weekly Super Chef sessions

Rounds	Objective	Individualized activity
Transition	Self-regulation and arrival into the session	
Activity 1	Sharing cooking experiences	
Activity 2	Preparation for cooking and food exploration	Every session
Snack time	Practicing small-talk and turn-taking in unstructured conversation, participating in games and activities	

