### Adverse effects

Even in the presence of significant group differences, some evidence suggests that psychological interventions such as SSGT may not be universally effective, with the chance that a minority of the participants may not benefit or even be harmed by the intervention [82]. This poses a significant problem and is an area of concern that is often overlooked [98]. While several studies have attempted to capture the adverse events related to a SSGT interventions [9, 17, 35], no study has investigated these effects fully. The present study will address this limitation, asking the adolescents themselves if they experienced any negative feelings or events during or after their involvement in either programme (as measured by the NEQ). These data will provide evidence of the frequency and characteristics of adverse effects enabling refinement of future SSGT programmes.

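### The NEQ is described as covering the intervention period only, yet the Discussion relies on it for negative events after involvement; as written, the 12 weeks to the primary endpoint have no designated harms measure

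*Protocol article*

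**What the plan says.** Two sections of the protocol article describe the Negative Incidents and Effects of Psychological Treatment questionnaire (NEQ).

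- **Methods, Secondary outcome measures.** The NEQ "assesses potential adverse and unwanted events associated with attending the groups at the completion of each programme, via adolescent self-report". Its 32 items ask adolescents to grade "any negative events experienced during the intervention period, asking participants to attribute their causality to either the programme or external circumstances".
- **Discussion, Adverse effects.** The trial will improve on earlier work by asking the adolescents themselves "if they experienced any negative feelings or events during or after their involvement in either programme (as measured by the NEQ").

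The Design section places the primary endpoint "at follow-up, 12 weeks following the intervention (primary endpoint"), and Data collection repeats this. The Table 3 legend lists the NEQ and defines T3 as post-intervention and T4 as follow-up. The grid that would show when each measure is given is not available.

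Other parts of the article bear on the weeks after the programme:

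- Daily Experience Sampling Method (ESM) texts to adolescents and parents continue until the final follow-up.
- Outcome scales are collected at follow-up, subject to Table 3.
- Process-evaluation interviews take place when the programmes end.
- The Participants section says that families are told, at consent, what to do if an adverse event occurs.

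**The concern.** Both sections name the same instrument but give it different coverage. A questionnaire completed when the programme ends, about the period of the programme, cannot record what happens afterwards. The Discussion says it will.

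Benefit is judged 12 weeks after the programme. Negative effects that appear only once the group has stopped, such as the loss of a regular peer group or a failed attempt to use a taught skill, fall outside the NEQ as Methods describes it. The article presents its harms data as an advance on earlier trials, and its Conclusion lists the measurement of negative effects among the study's contributions. Any published statement about harms after involvement would lack data from the instrument cited for it.

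**Working it through.** The plan gives no figure on this point to reproduce. The check compares the texts and then does one short calculation.

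**Step 1: the two descriptions side by side.**

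| Feature | Methods (Secondary outcome measures) | Discussion (Adverse effects) |
|---|---|---|
| Instrument | NEQ | NEQ |
| When given | Programme completion | Not stated |
| Period asked about | Intervention period | During involvement and after it |
| Cause asked about | Yes, programme or external | Not stated |

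The periods differ. For a participant who completes the programme, involvement ends when the programme ends, so anything after involvement lies outside the Methods window.

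**Step 2: does the missing Table 3 grid settle it?** There are two possibilities.

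- The grid lists the NEQ at T3 only. The Discussion then promises something the schedule does not deliver.
- The grid lists the NEQ at T3 and T4. The Methods timing is then incomplete. A T4 form that asked about "any negative events experienced during the intervention period" would still leave out the 12 weeks before it.

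Either way, at least one section needs correcting.

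**Step 3: does another described measure fill the gap?**

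- ESM: daily to follow-up, but it rates five emotional states. It does not ask about events or their cause, and the article presents it as a measure of everyday quality of life.
- Follow-up scales (for example loneliness, social anxiety, quality of life): these can show worsening by arm, but they are outcome measures and do not ask about attribution.
- Process interviews: held at programme completion, so they do not reach the later weeks.
- Consent information: shows that families receive directions, but the article describes no recording or analysis of the events.

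None of these is designated as a harms measure.

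**Step 4: share of time outside the NEQ window as Methods describes it.**

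Inputs:

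- follow-up interval, 12 weeks (Design)
- programme length, 16 weeks: "following the completion of the 16-week intervention (post-intervention") (Data collection)
- pilot delivery: "16 sessions in 20 weeks, with two 8-week session blocks interspersed with the Australian school holidays" (The interventions)
- study duration, 9 months including follow-up (Cost data analyses), taken as 9 × 52/12 = 39 weeks

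Formula: share = 12 / (total weeks).

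- 16-week programme: 12 / (16 + 12) = 12/28 = 0.43
- 20-week delivery: 12 / (20 + 12) = 12/32 = 0.375, about 38%
- Nine-month study: 12/39 = 0.31

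The share applies to both arms and to all of the planned 90 or more participants.

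**The case against.** The strongest reply has five parts.

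1. **The schedule cannot be read.** Methods places the NEQ at completion but does not say that it is given only then. A reader might infer a single administration. The documents do not establish that, because the Table 3 grid is not shown, and the Discussion's wording would fit a T4 administration. This stands. It does not remove the mismatch, because the recall window in Methods would be wrong even with a T4 entry.
2. **The 12 weeks are not unobserved.** A reader might infer that participants go unmonitored. That is too strong. Daily ratings of sadness, loneliness, anger, fear and anxiety continue to follow-up, and randomisation allows a comparison of these and the follow-up scales between arms. Loss of the peer group could well show there. This stands. What is missing is narrower: a designated harms measure that asks about events and their cause.
3. **The claim to investigate harms more fully.** A reader might take this as a promise about length of follow-up. In context the remedy offered is to ask adolescents directly, so that sentence need not be withdrawn.
4. **The Discussion phrase may concern early leavers.** Participants who do not finish are still approached for questionnaires, so time after they left but before programme end could count as after involvement. That gives the phrase some content for dropouts, but none for completers.
5. **Asking at programme end is a legitimate choice, and no benefit-harm balance at the primary endpoint is promised.** Both are true. If that choice is intended, the Discussion should describe it accordingly.

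The article also condenses a fuller protocol, which may hold further adverse-event procedures. The point therefore rests on two explicit statements that disagree and not on missing detail.

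**Conclusion.** The point holds as an inconsistency with a practical consequence. The Methods description of the NEQ cannot deliver the harms coverage that the Discussion attributes to it. If Methods is followed, the 12 weeks before the primary endpoint have no designated harms measure with causal attribution: 43% of the time from group start with a 16-week programme, 38% with 20-week delivery, and about 31% of the nine-month study. These are shares of elapsed time, not estimates of missed events, and they assume that no NEQ with a post-programme window is given at T4.

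The documents do not support saying that the NEQ is given only once, or that participants are unmonitored after the programme. The primary efficacy analysis is unaffected. What changes is what the trial can say about harms after the programme ends, and the remedy is cheap enough to be worth making.

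**What to change.** Preferred change:

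- Give the NEQ at T4 as well as T3, with the T4 questions covering the time since the end of the programme.
- Report T3 and T4 harms separately by arm.
- Amend the NEQ paragraph in Secondary outcome measures to state both time points and both recall windows, and make the Adverse effects section and Table 3 agree with it. If Table 3 already lists T4, only the Methods timing and window need correcting.

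The cost is one existing 32-item self-report form at a follow-up assessment that already takes place: a few more minutes for each adolescent, with no new visit or staff.

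If T4 is not used, remove the words *or after* from the Adverse effects section and state that NEQ-reported harms are known only to programme end. That costs nothing but gives up any NEQ-based statement about harms in the 12 weeks before the primary endpoint.
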